## Abstract

Many men have poor mental health and need help to recover. However, designing a rehabilitation intervention that appeals to men is challenging. This study protocol aims to describe the ‘Wildman Programme’, which will be a nature-based rehabilitation programme for men on long-term sick leave due to health problems such as stress, anxiety, depression, post-cancer and chronic cancer, chronic obstructive pulmonary disease (COPD), cardiovascular disease, or diabetes type II. The programme will be a nature-based rehabilitation initiative combining nature experiences, attention training, body awareness training, and supporting community spirit. The aim of the study will be to examine whether the ‘Wildman Programme’ can help to increase quality of life and reduce stress among men with health problems compared to treatment as usual. The study will be a matched control study where an intervention group (number of respondents, *N* = 52) participating in a 12-week nature-based intervention will be compared to a control group (*N* = 52) receiving treatment as usual. Outcomes are measured at baseline (T1), post-treatment (T2), and at follow up 6 months post-intervention (T3). The results of this study will be important to state whether the method in the ‘Wildman Programme’ can be implemented as a rehabilitation offer in the Danish Healthcare System to help men with different health problems.

## 1. Introduction

The prevalence of people in Denmark experiencing high levels of stress has increased from 20.8% in 2010 to 25.1% in 2017 [1]. Poor mental health and other mental disorders are also increasing problems in the Danish population.

Far more women than men experiencing stress and stress-related diseases seek help in the Danish healthcare system [2,3]. A possible explanation is that the Danish healthcare system lacks attractive rehabilitation interventions for men [3]. Another possible barrier can be the view of men in the Danish culture. Many men feel they are not allowed to be vulnerable, and therefore, it can be difficult for them to reach out for help when they go through a life crisis [2,4].

### 1.1. Rehabilitation In Natural Environments

Since ancient times, there has been a belief that certain natural areas possess special qualities that can bestow delectation and health for a troubled soul. Already in the Gilgamesh epic, written almost 5000 years ago, it is told how King Gilgamesh could find consolation, strength, and health in a magnificent garden [5]. In sacred writings such as the Bible and the Quran, in the poems of the Roman author Vergilius and in countless poems, novels, and songs thereafter, the longing for pleasant natural environments has been expressed. However, throughout this time, there has also been descriptions of unpleasant and unhealthy natural areas, where some even provoke horror that people shun. Divina Commedia by Dante Alighieri (1320) [6] describes Hell in images of stinging insects, storms, swamps, iciness, darkness, red hot deserts, and choking gases. Research has shown that humans reflexively avoid certain places and situations [7,8], while others are attractive [9,10].

The word “nature” derives from the Latin “natura”, which literally means “birth”. Early on, the word gained a broad significance, in being the basis or inherent quality of individual things or persons as well as life on earth or the universe [11]. The word “culture” derives from Latin’s “cultura”, which means “cultivate”, but also figuratively “care and honoring”, where “cultura” originates from Latin’s “colore” which means “to tend” and “guard” [11]. Thomas Beck [12] writes about the two Renaissance philosophers Jacopo Bonfadio and Bartolomeo Taegio. Both published in the mid-16th century thoughts on how nature should be described and interpreted. They defined the wilderness as the first nature, the cultural landscape with fields and pastures as the second nature, and the garden as the third nature. Beck claims that their thoughts were not new but had already been described in ancient Rome by, for example, Pliny the Elder, Lucretius, and Cicero. The third nature represents the finest interaction between nature and culture, not least art and nature, according to Bonfadio and Taegio [12]. In landscape architecture, this definition of nature has been strong. Today, especially the first nature is seen as threatened, but also the second and third nature. This has led to talk of a fourth nature, to recreate environments with high biodiversity, both in urban areas and in rural areas [13]. Kronlid writes on the view of the first nature that a survey among landscape architects shows that it can be divided into three parts: the “free nature”, completely free to develop under its own conditions without being contaminated by visible human influence; the “non-free nature” that is used to satisfy needs in, for example, tourism and recreation as well as a type of “false nature”, a false construct, completely subordinate to human influence as a production landscape of, for example, timber and other raw materials [14]. This tradition is also strong in environmental psychology, and not least where environmental psychology, landscape architecture, and nature’s impact on health are combined; e.g., when it comes to nature-based rehabilitation. Terry Hartig and colleagues write the following: ”We are particularly concerned with nature as the seemingly natural features and processes that people ordinarily can perceive without the use of specialised instruments or sensory aids. (…) the terms ‘nature’ and ‘natural environment’ get used somewhat interchangeably, although, in a seeming contradiction, the nature of interest here is not only found in natural environments, but also in otherwise built environments. (…) People may enjoy urban parks, botanical gardens, and golf courses as representations of natural environments, while still knowing of their artificial character” [15]. More research is exploring the health promoting qualities in nature and which qualities have most effect regarding e.g., age, gender, or health; at work or leisure; in schools, hospitals, at home, etc. One of the ways to describe these qualities is by the Perceived Sensory Dimensions (PSD) [16].

Previous research suggests that spending time in natural environments and using nature therapy in rehabilitation programmes can increase quality of life, reduce symptoms of heart disease [17,18], relieve symptoms of stress [18,19,20,21,22], reduce symptoms of anxiety and depression [23], and increase the ability to return to work after sick leave [24]. Most of these studies have been conducted in more urban green areas and gardens. However, studies have also been conducted in forest areas outside built-up areas. A large number of scientific studies suggest that forest therapy is a beneficial intervention in reducing stress levels and depression in adults. However, most studies are not sufficiently well accomplished regarding control groups and accuracy [25,26].

Given that natural environments cause different emotions, how come humans do recover from high levels of stress and mental fatigue in these environments [27]? Research show that people seem to have an innate ability to feel danger or security in natural environments. Two theories start from this evolutionary perspective: The Stress Reduction Theory (SRT) [28,29] and the Attention Restoration Theory (ART) [30]. Both of these theories are developed to explain why, for example, walking in urban green areas restores humans from high levels of stress and mental fatigue.

SRT was developed by the American environmental psychologist Roger Ulrich [28]. Ulrich argues that despite most of us live in urban environments, the human genome is identical to our ancestors. Back in more primitive ages, man was subject to the terms of nature and forced to trust his basic emotions, i.e., his unconscious and instinctive bodily reactions. Today, in urban environments, we are bombarded with information most of the time, and our basic emotions are not adapted to these new living conditions. This can cause affective hyperactivity and difficulties with emotional regulation that can lead to stress, anxiety, and depression. In natural environments, compared to urban environments, it is easier for us to judge when a threat is over, which makes it possible for our body and mind to release the sympathetic stress response after a threat and subsequently relax and recover. However, it is important that the natural environments are experienced without threats when it comes to recovery and healing. Nature without threats automatically causes positive feelings and a parasympathetic physiological response that is associated with feelings of calmness, relaxation, comfort, and fascination [28,31].

ART was developed by the two psychologists Stephen Kaplan and Rachel Kaplan and describes attention processes that take place in nature. These processes occur on a perceptual cognitive level and have a recovering effect. The theory describes the healing effect of nature and defines two different kinds of attention: (1) directed attention and (2) soft fascination. We switch between the two kinds of attention during our everyday life according to our present tasks and environment [32,33]. The ART theory is based on the assumption that people have two systems of attention: directed attention and fascination. Directed attention is used when we work in a goal-oriented way and need to inhibit distractors, i.e., when driving a car or working in an office. This requires a huge amount of energy and is an exhaustive resource involved in executive processes in thinking and may lead to directed attention fatigue [34]. Fascination catches our attention involuntary, and we do not need to or can decide when to use it. Fascination can be hard, i.e., what catches the attention leaves no room for reflection. For example, it may be that you are watching an exciting competition in sports. However, in nature, most of the things you experience are of a soft character. You may see a gleam of water or hear a bird singing. It does not require tiring decisions; instead, you can rest in the experience. This increases our mental capacity and has a restoring and recovering effect on our body and mind [32]. According to ART, our senses are stimulated in nature and here, we automatically use the soft fascination, which means we can relax and rest. The theory has been tested in many studies with encouraging results [35,36]. However, there are criticisms of some assumptions, such as the evolutionary basis of the mechanism and the definition of soft fascination [37].

Both theories, SRT and ART, are based on evolutionary theory. They claim that not all natural areas are restorative. The restorative natural environments should contain special characteristics that most people interpret as safe and restful, and the theories involve a number of such qualities [29,32].

A theory based on nature-based interventions with staff and which has the potential to be developed further is the Supportive Environment Theory (SET) [27,38,39]. The theory incorporates the theories SRT and ART and deals with synergies between the capacity of natural areas to heal people and the professional knowledge of the staff. SET was developed by the Swedish Professor and landscape architect [name], and it focuses specifically on the treatment of stress-related mental illnesses in therapy gardens [24,40]. SET describes which qualities of natural environments we prefer and where we feel safe [16]. In these safe environments, we are able to relax and recover. SET is a biopsychosocial theory [41] based on the evolutionary assumption that human beings have evolved in close contact with natural environments living in small social and cultural communities. Since we have evolved this way, we find some environments inherently more supportive than others. Supportive environments have physical (both built and natural environments), social (e.g., relatives, friends, or colleagues), and cultural (e.g., values, historical context, traditions) qualities. According to SET, we need supportive environments to develop physically and mentally [38]. Research on long-term nature-based supportive environmental rehabilitation programmes (up to a duration of 24 weeks) shows better results and a reduction in symptoms of stress and depression in the participants and an increase in the participants’ return to work [24]. SET proposes the development of health-promoting synergies regarding support from the three different spheres (the social, cultural, and physical environment) through activities led by a professional staff.

In this context, the following are of interest to highlight: Research shows that meditation and breathing exercises can activate the parasympathetic nervous system and help reduce symptoms of stress [42] and depression [43,44], and they can be used in nature-based therapy with positive results for health and well-being [45,46,47] In addition, a systematic review shows that combining breathing exercises and body awareness training such as Qigong can enhance mental health [48,49]. Research in the field of Qigong shows that higher levels of energy and better body awareness can have a positive impact on the participants’ mental and physical health [49].

Furthermore, ecotherapy [50] can help strengthen the social sphere; the community feeling [51] and being part of a social community with others can enhance feelings of meaning and life purpose [52]. The creation of a common meaning and a sense of coherence in the group can improve the participants’ health and quality of life [52]. Ecotherapy suggests that many people today need to rebuild their contact with nature and that sensory experiences in nature can activate the parasympathetic nervous system and help to restore the body and mind. For example, focusing on the different sensory experiences in nature, such as scents, sounds, tactile stimuli of nature objects and focus on details as well as the wholeness of nature’s diversity gives a sense of well-being [50,51]. According to SRT, it is easier for people to interpret and value sensory experiences from nature [28,29].

### 1.2. The Wildman Programme

A Swedish study shows that the interest in outdoor life among people in Sweden is great in relation to forests, beaches, the sea, meadows and hills, regardless of age and ethnicity. There are, of course, differences between the groups when it comes to outdoor life. For example, people aged 45–64 visit natural environments more often than those who are 25–44 years old; those who live in the countryside visit natural environments more often than people living in the cities; and people born outside Europe visit natural environments less often than those born in Europe. The interest in outdoor life is nevertheless great. For example, 57.2% of those born outside Europe visit natural environments frequently or very often, while the corresponding figures for those born in Europe are 67.5%. We must assume that it is the same in Denmark [53]. Nature-based interventions in gardens, such as horticultural therapy, mostly attract women [24]. In various studies, men have shown a strong interest in the wilderness and activities in the wilderness, including multi-day trips with overnight stays [54]. A North American study found that the difference between various ages and ethnic groups among men was relatively small [55]. Interest has been relatively constant since the 1980s [56], and it is not the lowest among men in northern Europe [57]. The value lies in the challenges being concrete and perceived as meaningful. If they are manageable, the participants experience a reward; for example, it may be about coming to a place experienced as beautiful and breath-taking [58]. In an effort to offer a rehabilitation programme that appeals more to men, we developed the ‘Wildman Programme’. The ‘Wildman Programme’ is a nature-based rehabilitation initiative (NBR) combining nature experiences in rural settings (presentation of scenic areas, sensory activities, silent walking, and fascinating stories about nature and how we are connected to the big circle of life), attention training (walking, standing, sitting and lying meditations, outdoor sittings, and narrative meditations), body awareness training (breathing exercises, outdoor playing, balance training, Qigong, and other kinds of physical activities), and supporting community spirit (bonfire cooking, talks, and storytelling around the bonfire). The overall goal of the programme is to improve quality of life and reduce symptoms of stress among the participants. The ‘Wildman Programme’ is designed to appeal to men, and especially to men who do not feel motivated to participate in other rehabilitation programs. If this program proves to work, it can broaden the range of rehabilitation measures for men. The approach of the programme is inspired by the SET theory, including ART, SRT, ecotherapy, and activities such as meditation and Qigong. In addition, the men are introduced to knowledge from evolutionary theories, which explain how still today in modern society we have to rely on the instincts and basic emotions we had when we lived as hunters and gatherers in nature many thousands of years ago.

We believe that one of the problems in modern Western societies today is that we have disconnected ourselves from nature, and that makes us sick. Rebuilding the connection with nature is important for our well-being, since we have always lived in close contact with nature. Nature connection, as we define it, includes place attachment. It is about the interaction between person, process, and place and contains both cognitive, affective, and behavioural components. The person in question must feel that the place and the activities it invites provide security, meaning, and involve a flow of self-rewarding activities that can bestow a moment of happiness [59,60,61,62]. The evolutionary explanation, which can be related to the theories above, we assume can motivate the participants in the ‘Wildman Programme’ and inspire them to feel hope for the future and get back in contact with their inner strengths, which are feelings the participants have often been missing for a very long time because of symptoms of stress and health problems. Understanding our evolutionary connection to nature and how our body and mind are adapted to live close to nature can, according to e.g., Jordan and Hints [51], reduce stress and improve quality of life.

### 1.3. Aim

The aim of the present study is to investigate the effect of a nature-based intervention ‘The Wildman Programme’ on quality of life and symptoms of stress among men with long-term health problems compared to men receiving treatment as usual. A further aim is to investigate which natural environments in rural areas work best as supportive environments in rehabilitation. The purpose of this study protocol is to inform about the study and how it is intended to be conducted. Moreover, through the review process, the design and focus of the study can be improved.

Our expectation is that nature-based rehabilitation is suitable for men with depression and stress or long-term illnesses that can lead to depression and stress, and that the nature-based ‘Wildman Programme’ accordingly can help men with a wide variety of chronic illnesses.

Thus, we expect that the participants receiving the intervention will first and foremost experience a significant improvement in their quality of life measured by the World Health Organization Quality of Life Instruments (WHOQOL-BREF) scale [63] corresponding to a 20% improvement. WHOQOL-BREF is an abbreviated generic Quality of Life Scale developed through the World Health Organization.

Furthermore, we assume significant improvements in the other secondary effect outcomes (symptoms of stress, self-experienced restitution, and return to job) compared to the participants receiving treatment as usual (TAU). As far as we know, this type of intervention or research has never been conducted before.

## 2. Materials and Methods

We choose to conduct the study as a matched-controlled study. An intervention group is receiving nature-based therapy through the ‘Wildman Programme’ and will be compared to a matched control group receiving TAU i.e., case management (see Figure 1). Participation in the ‘Wildman Programme’ is voluntary, and the study has been ethical approved by the University of Southern Denmark Research & Innovation Organization, SDU RIO.

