### 2.2. Participants

Inclusion criteria: The participants are men, aged 18–76 years old, living in the region of southern Funen in Denmark. The male participants are on long-term sick-leave and suffer from stress (ICD: F43.8 and F43.9), anxiety (ICD: F41.2), or depression (ICD: F32.0) according to the ICD, the International Classification of Diseases [68]. Moreover, the participants can suffer from diseases such as chronic cancer, post-cancer, chronic obstructive pulmonary disease (COPD), cardiovascular disease, or type 2 diabetes—all of which can cause stress. We expect that the nature-based ‘Wildman Programme’ can help men with a wide variety of chronic illnesses improve their quality of life and reduce symptoms of stress. Many of the participating men included in the study will in the beginning of the course to some extend experience lower quality of life and not have benefitted sufficiently from participation in other available rehabilitation interventions.

The participants will be divided into groups of 10–18 individuals in the ‘Wildman Programme’. Approximately 40% of the participants will be recruited from the health centre in the Municipality of Svendborg and the Municipality of Faaborg-Midtfyn, approximately 40% will be recruited from the jobcentre in the Municipality of Svendborg and the Municipality of Faaborg-Midtfyn, and the remaining 20% will be recruited from the general practitioners. The control group will be recruited as a form of a natural experiment from comparable departments in the health centre and the job centre and from other general practitioners.

The study will include at least 104 participants: 52 in the intervention group and 52 in the control group. The diagnoses, ages, job status, and social status of the participants will be recorded. Instead of selecting participants to be included in the intervention group and TAU by randomisation, we have chosen to follow two groups via a type of natural experiment or quasi-experiment. We choose to select the TAU group from matched health centres, job centres, and general practitioners via their normal standard routines, where the groups are matched with respect to age, gender, and diagnosis [69]. The matched control group (*N* = 52) of men will resemble the men in the intervention group with regard to the distribution of age, job status, and levels of stress to ensure that the participants in the intervention and control group are as similar as possible (see Figure 2).

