The participants in the control group receive traditional treatment and rehabilitation in the healthcare system of the municipalities, which do not take place in nature. They participate in physiotherapeutic treatment, fitness training, mindfulness courses, and traditional rehabilitation programmes (consisting of e.g., physical exercise, nutritional counselling, and education about their illness).

The exclusion criteria are psychosis or psychotic disorders, brain injuries, addiction or physical disabilities that prevent them from participating in the physical exercise programme or move about in nature.

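### Treatment as usual is described as case management in one place and as active rehabilitation in another, and rehabilitation history is neither matched on nor listed for recording

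*Protocol article*

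**What the plan says.** **The comparator.** The opening of section 2 (Materials and Methods) says the programme group "will be compared to a matched control group receiving TAU i.e., case management". The "i.e." makes this a definition, not an example. Section 2.2 (Participants) describes the same group differently: "The participants in the control group receive traditional treatment and rehabilitation in the healthcare system of the municipalities, which do not take place in nature". It then lists the content: "They participate in physiotherapeutic treatment, fitness training, mindfulness courses, and traditional rehabilitation programmes".

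**The programme men.** Section 1.2 says the programme is designed to appeal to men, "especially to men who do not feel motivated to participate in other rehabilitation programs". Section 2.2 says: "Many of the participating men included in the study will in the beginning of the course to some extend experience lower quality of life", and the same sentence adds that they will "not have benefitted sufficiently from participation in other available rehabilitation interventions".

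**How controls are chosen.** Section 2.2 gives the source of controls: "We choose to select the TAU group from matched health centres, job centres, and general practitioners via their normal standard routines". On the matching variables, the section states that "the groups are matched with respect to age, gender, and diagnosis". It then says the control men will resemble the programme men in age, job status and stress level. The characteristics listed for recording are diagnosis, age, job status and social status. Allocation is not randomised, with 52 men planned in each group.

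**The concern.** Section 1.3 sets the aim as the effect of the programme compared with treatment as usual, so the definition of TAU fixes what is being estimated. If controls receive case management, the trial asks whether the programme does better than coordination of a man's case. If they receive physiotherapy, training, mindfulness and rehabilitation courses, it asks whether nature-based rehabilitation does better than conventional rehabilitation. The same observed difference would support different conclusions, and sections 4 and 4.2 intend to use the result to argue for implementation in Danish municipalities.

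The second issue is comparability. The article itself names a feature of programme men, a poor fit with or insufficient benefit from other rehabilitation, that could plausibly relate to later quality of life. It describes controls as men who take part in such care. If rehabilitation history differs between the groups and is not recorded, the analysis can neither show the imbalance nor adjust for it.

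**Working it through.** The plan attaches no figure to this point, so the check is mainly a comparison of passages. A short illustration of scale follows.

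**1. Is TAU stated in two ways?**

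| Place | Care given to controls |
|---|---|
| Section 2, opening | Case management |
| Section 2.2 | Physiotherapy, fitness training, mindfulness courses, rehabilitation programmes |
| Section 4.1 | Control values assumed similar to those in ordinary rehabilitation |

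Case management could be the framework through which the care in section 2.2 is arranged, but no sentence says so. The conflict therefore stands in the text.

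**2. Is rehabilitation history covered anywhere?**

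| List | Variables | Rehabilitation history? |
|---|---|---|
| Matching (2.2, repeated in 4.1) | Age, gender, diagnosis | No |
| Resemblance (2.2) | Age, job status, stress level | No |
| Recorded (2.2) | Diagnosis, age, job status, social status | No |
| Questionnaire (3.1) | WHOQOL-BREF, PSS, PRS-11, job status | No |

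Section 4.1 concedes in general terms that comparability cannot be safely determined. It does not mention rehabilitation history.

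**3. How far do the statements about programme men go?** Section 2.2 says many, not all. It says insufficient benefit, not none. It does not identify the other interventions, and it is not an entry criterion. Section 1.2 describes whom the programme should attract, not who is enrolled. These statements support a possible imbalance and do not establish one.

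**4. Scale, as an illustration.** Inputs from section 3.2: SD 18.0, two-sided 5% assumed (sidedness is not stated), dropout 15%, d = 0.60.

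- Check of the plan's own number. The two-sample t-test at d = 0.60 and 80% power needs 45 per arm. Then 45 × 1.15 = 51.75, so 52 per arm and 104 in total; 45 / 0.85 = 52.9, so 53 per arm and 106 in total. The stated 104 is reproduced within rounding and the choice of dropout formula.
- Completers: 52 × 0.85 = 44.2, taken as 44 per arm.
- Standard error of the difference: 18 × √(2/44) = 3.84 points.

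Suppose the programme has no effect beyond TAU and the arms differ by b points only because of rehabilitation history. The chance of a significant t-test is:

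| b (points) | b / 18 | P(significant) |
|---|---|---|
| 0 | 0 | 5% |
| 2 | 0.11 | 8% |
| 4 | 0.22 | 18% |
| 6 | 0.33 | 34% |

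The bias could equally run against the programme. With a true difference of 0.60 × 18 = 10.8 points, power is 79%. If confounding hides 1.8 points, 9.0 remain and power is 64%. If it hides 4.8, 6.0 remain and power is 34%.

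The values of b are assumptions. The calculation uses the simple t-test of the sample-size section, not the planned mixed model. The mixed model uses the T1 scores, which may absorb part of a difference in level but not a difference in later course.

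**The case against.** The strongest reply is that the opening of section 2 is shorthand and section 2.2 is the full description: case management is the municipal framework, and the listed activities are its content. That is plausible, but the article does not say it, and the shorthand is worded as a definition. Both passages describe what one control group receives, so they do not show two populations. Nor do they leave a recruiter unable to judge eligibility, which rests on the criteria in section 2.2. That part of the reply stands.

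It can also be said that non-comparability is already admitted in section 4.1, and that diagnosis, job status and stress level may capture part of any difference in history. Both are fair. Neither replaces measuring a characteristic that the authors themselves single out.

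A reader might infer three stronger things, and the documents support none of them.

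- *That the arms do enter in different care states.* The controls' rehabilitation history is not described, and the statement about programme men covers many of them, not all.
- *That controls are measured partway through a course, so part of their gain precedes T1.* Nothing says so. The exact timing of control T1 is operational detail that an article may leave to a fuller protocol.
- *That the contrast is inflated by a third to a half.* That figure needs an assumed effect of usual rehabilitation of 0.2 to 0.3 SD. It is then only 0.2/0.6 = 33% and 0.3/0.6 = 50%. Its direction is not established either: men who have already failed to benefit may be harder to improve, which would shrink the contrast.

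**Conclusion.** The point holds in two parts. First, the comparator is stated in two incompatible ways, and the passages must be reconciled, because they decide which question the trial answers. This rests on the text alone. Second, rehabilitation history is an unmatched and, on the stated lists, unrecorded potential confounder in a non-randomised comparison. Its size and direction are unknown. The figures of 8%, 18% and 34% show only what differences of 2, 4 and 6 points would do at SD 18 and 44 completers per arm, and are not estimates of bias in this trial. Different care states at entry, mid-course control baselines and an inflated contrast remain possibilities, not findings. A fuller protocol that is not shown may record rehabilitation history. It would not remove the conflict over TAU within this article.

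**What to change.** - **Definition.** Reconcile section 2 and section 2.2 into one statement of TAU, used throughout. Which description is right is for the investigators to say.
- **T1 items in both arms.** Ask about prior and current rehabilitation for the present problem, and whether it helped. Word the items to cover care up to T1, so that the covariate does not absorb the TAU being compared. Tabulate the answers by arm.
- **Analysis.** Add this history as a covariate in the linear mixed-effects model. If the arms barely overlap on it, say so, because adjustment then rests on extrapolation.
- **Care received.** Record which usual care each control receives between T1 and T3, and word the conclusion against that care.

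The cost is some protocol wording, a few questionnaire items and one more covariate. Restricting controls to men just starting care, with a matched rehabilitation history, is not needed for this fix. It would be a debatable change to the natural-experiment design the authors chose. The definition and the T1 items should be settled before enrolment, since baseline history can afterwards be recovered only from recall.
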